## Abstract

**Background:**

In countries with a high burden of HIV, such as South Africa, where the epidemic remains the world’s largest, improving early uptake of and consistent adherence to antiretroviral therapy could bring substantial HIV prevention gains. However, patients are not linked to or retained in care at rates needed to curtail the epidemic. Two strategies that have demonstrated a potential to stem losses along the HIV care cascade in the sub-Saharan African context are use of text messaging or short message service (SMS) and peer-navigation services.

**Methods/Design:**

We designed a cluster randomized trial to assess the efficacy of an SMS intervention and a peer-navigation intervention to improve retention in care and treatment, timely linkage to care and treatment, medication adherence, and prevention behaviors in South Africa. Eighteen primary and community healthcare clinics in Rustenburg and Moses Kotane Sub-districts in the North West Province were randomized to one of three conditions: SMS intervention (n = 7), peer navigation intervention (n = 7), or standard of care (n = 4). Approximately 42 participants are being recruited at each clinic, which will result in a target of 750 participants. Eligible participants include patients accessing HIV testing or care in a study clinic, recently diagnosed with HIV, aged 18 years or older, and with access to a cellular telephone where they are willing to receive automated SMS with HIV-related messaging. Data collection includes extraction of visit information from clinical files and participant surveys at baseline, 6 months, and 12 months. Intent-to-treat (ITT) analysis will explore differences between randomization arms and the primary outcome of patient retention in care at 12 months following enrollment. We will also explore secondary outcomes including participants’ a) timely linkage to care (within 3 months of HIV diagnosis), b) adherence to treatment based on self-report and clinic’s medication dispensation dates, and c) condom-use behaviors.

**Discussion:**

The findings will allow us to compare the efficacy of two complementary interventions, one that requires fewer resources to implement (SMS) and one (peer navigation) that offers more flexibility in terms of the patient barriers to care that it can address.

**Trial registration:**

NCT02417233, registered 12 December 2014.

## Background

The success of “treatment-as-prevention” trials has ushered in a new era in worldwide HIV prevention efforts [1]. Antiretroviral therapy (ART) suppresses viral replication, effectively forestalling disease progression and reducing the likelihood of viral transmission [2–6]. The landmark HPTN 052 trial among HIV sero-discordant couples found that early ART initiation (when CD4+ cell count is between 350 and 500 cells/μL) can reduce HIV transmission to uninfected partners by 96 % [2]. In countries with a high burden of disease, such as South Africa, where the epidemic remains the world’s largest with an estimated 6.4 million people living with HIV (PLHIV) [7], improving early uptake of and adherence to ART could bring substantial gains in HIV prevention. Modeling suggests that annual HIV testing with the immediate initiation of ART (at any CD4 count) in South Africa could reduce HIV incidence and mortality to less than one case per 1000 people per year by 2016 [8]. Additionally, South Africans residing in communities with greater ART coverage have a lower risk of HIV acquisition [9]. While instituting universal ART coverage will be challenging to implement in resource-constrained settings, important gains can be attained by ensuring that infected individuals are identified early in their HIV disease, enter into care rapidly, and remain in care and adherent to their regimens following the initiation of treatment. Unfortunately, in sub-Saharan Africa, some 40 % of individuals who test positive are not successfully linked to care, and only 50 % of those who are not yet ART-eligible are retained in HIV care [10], leading to a “cascade” of losses at each stage along the care continuum [11].

In South Africa, the government continues to sponsor national HIV testing campaigns and has expanded ART eligibility, first to those with a CD4+ cell count of 350 cells/μL or less and recently to those with a CD4+ cell count of 500 cells/μL or less [12, 13]. Although treatment expansion is critical, current losses along the HIV care cascade are impeding HIV prevention gains. National data from 2012 indicated that 65 % of the population had been tested for HIV; however, only 37.8 % of HIV-positive men and 55 % of HIV positive women were aware of their HIV status [7]. Additionally, once diagnosed, many do not initiate care or treatment. A study in Cape Town found that only 62.5 % of recently diagnosed patients received a CD4+ test result within 6 months; 66.7 % of those that were eligible for ART initiated treatment; and only 46.3 % of those not ART eligible returned for a subsequent CD4+ test [14]. In a study in rural Kwa-Zulu Natal, only 44.9 % of the HIV-positive patients not yet ART eligible returned for subsequent CD4+ tests within 13 months [15]. To summarize, whereas South Africa has the largest antiretroviral program in the world [16], only 52 % of patients eligible for ART are estimated to currently receive treatment [17]. These failures to engage patients in care are exacerbated by further considering loss to follow-up after ART initiation, which has long-lasting implications, worsening outcomes for PLHIV, even if they return to care [18].

Interventions that link and retain patients in HIV care, promote ART adherence, and encourage risk-reduction behaviors in resource-limited settings are essential and could substantially improve survival and prevent new HIV infections [2, 19, 20]. We sought to identify strategies that do not require extensive resources and could realistically be implemented and supported by health departments in sub-Saharan Africa. Among feasible strategies that have the potential to improve care engagement outcomes, particularly retention and adherence, text messaging or short message service (SMS) and personal support have both demonstrated promise and could be economically feasible [20–22]. SMS cost 1 to 2 cents to send in bulk and are free for clients to receive. Systematic reviews and meta-analyses have demonstrated that the use of SMS for appointment reminders have improved clinic attendance [23–25]. Additionally, SMS interventions that included appointment reminders, laboratory result notifications, and medication reminders have demonstrated promise in improving ART initiation and retention in care, as well as ART adherence in African settings [26–29]. One randomized trial also demonstrated improved rates of viral suppression among those receiving weekly SMS [30].

Similarly, personal support interventions that focus on professional case management or engaging peers or family networks to provide encouragement and support to remain in care and adhere to medications have demonstrated promise [22]. A study in Kenya found that the time to treatment failure was longer (reflective of better retention and adherence to ART) for patients who participated in support groups, received pharmacy counseling, or who had home visits [31]. Research in Uganda suggests that care outcomes for those initiating ART and those still pre-ART can be improved when patients receive treatment support [32, 33]. Furthermore, recommendations from an international expert physician panel now call for systematic monitoring of linkage and retention in care, including the potential use of peer or paraprofessional patient navigators to assist patients in obtaining the care that they need [34]. Furthermore, peer navigators are less costly than professional personnel and may be more feasible to support in a resource-constrained setting.

Given the promise of these intervention options, we designed a cluster randomized trial to assess the efficacy of an SMS intervention and a peer navigation intervention to improve retention in care, timely linkage to care and treatment, ART adherence, and prevention behaviors in South African primary health clinics in the North West Province.

## Methods/Design

### Study design

Using a cluster randomized trial at the level of the clinic, we will evaluate the efficacy of employing two strategies for enhancing linkage to and retention in clinical care, ART adherence, and HIV preventive behaviors. A target of 750 participants will be enrolled across 18 clinics in the Moses Kotane and Rustenburg Sub-districts, Bojanala Platinum District, South Africa (Fig. 1). Clinics have been randomized to one of three conditions: an SMS intervention arm, a peer navigation (PN) arm that also includes SMS, and a control condition. Clinics have been randomized instead of individuals to avoid contamination of intervention across individuals within clinics and to facilitate cooperation with clinic staff. Participant outcomes will be monitored using both clinical record extraction to document HIV care visits and services and a series of interviewer-administered surveys at enrollment (baseline assessment), 6 months after baseline, and 12 months after baseline.

**Fig. 1 Fig1:**
[figure not shown]
Clinic allocation and participant enrollment. Notes: ^a^ Clinics were not eligible if they had a catchment area under 6,000 inhabitants, inadequate patient load to ensure recruitment targets (40 new patients to patient registers in the first 4 months of 2014), were pilot clinic sites (n = 4). ^b^ One clinic assigned to the SMS arm was under construction and has not opened as scheduled; as such, recruitment targets have been adjusted at the remaining SMS clinics. ^c^Participants are eligible if they are 18 or older, diagnosed with HIV within the last 12 months, receiving care at a study clinic, and willing to receive communication from study staff. Abbreviations used in the figure: No. = Number; PN = Peer Navigation; SMS = Short Message Service (i.e., Text Message); SOC = Standard of Care

### Study setting

The North West Province has a population of just over 3.5 million people. The province is disproportionately young, with 60 % of the population under the age of 34 years, with high rates of unemployment, poverty, and low levels of educational attainment. Over 46 % of the population is living in poverty compared to 39.9 % of the national average [35]. The province has the fourth highest HIV prevalence in the country: 13.3 % among the general population [7] and 29.7 % among women in antenatal services [36]. Within North West Province, the Bojanala Platinum District, representing 37 % of the overall provincial population, has an HIV prevalence of 35.0 % in the antenatal clinics [36], making it more heavily affected than most other districts. Care in Bojanala Platinum is provided by one provincial hospital, four district hospitals, 13 community health centers, 104 primary health clinics, and numerous mobile health points. Our study area was limited to two sub-districts, Moses Kotane and Rustenburg, and facilities included community health centers and primary health clinics only.

### Clinic selection and randomization

The 18 study clinics were selected from among 61 ART-initiating clinics within the two study sub-districts. To be eligible, a clinic could not be one of the four that had participated in a pilot test of the interventions, had to have a catchment area of 6,000 or more inhabitants, and have adequate patient load to ensure recruitment targets (defined as having 40 new individuals added to HIV patient care registers in the first 4 months of 2014). From among the 24 clinics meeting these criteria, we excluded one clinic that primarily served the mobile mining workforce (estimated at over 90 % of their patient load), and therefore was unlikely to retain patients. We also excluded one clinic that was not using patient registers, which precluded establishing eligibility; one clinic that was scheduled to close; and three clinics that were distant from study offices, complicating access and supervision.

The 18 remaining clinics were randomized to one of the three study arms, including seven to each intervention condition and four to standard of care (Fig. 1). The decision to randomize more clinics to intervention conditions was based on agreements with the local government partners at the district of health. We randomized sites using methods described by Hayes [37]. We stratified by sub-district and employed balanced (restricted) randomization based on number of total monthly clinic visits, number of HIV tests conducted in the previous four months, number of patients on ART, and the functionality of the monitoring and evaluation systems (including record-keeping and supply chain management) to ensure balance across the study arms.

### Participant eligibility and recruitment

We will be enrolling 750 participants, with a target of 42 (range = 30-55) participants at each facility. All participants must be diagnosed with HIV within 1 year preceding their enrollment. Participants must also be 18 years or older, have access to a cellular telephone where they are willing to receive automated text messages with HIV-related content, and be willing and able to give informed consent (not under the influence of illicit substances, or seemingly emotionally unstable at the time of recruitment and enrollment). Written informed consent will be obtained from all participants prior to enrollment in the study.

We aim to recruit an equivalent number of men and women and ensure that the sample has substantial representation (minimum of 30 %) of clients who do not yet quality for ART in order to assess the linkage and retention for both clients who initiate ART and those who do not. To accomplish this balance, recruitment will be completed using two strategies. The first strategy includes recruiting clients who present at the clinic for HIV testing and receive a positive diagnosis for the first time, or those who are returning to collect their initial CD4+ test results. Recruitment will be systematic: all of those presenting for an HIV test or for an initial CD4+ test result will be approached by clinic staff about their interest in participating in the study. We initially estimated that between 50 % and 60 % of those recruited during HIV testing would have an ART-qualifying CD4+ cell count at the time of recruitment [38]. Because the national guidelines have recently changed to increase qualifying CD4+ to 500 or less, it is more likely that 70 to 80 % of the individuals newly diagnosed after January 2015 will qualify for ART.

The second recruitment strategy includes identifying patients from recent entries in the HIV care registers at the clinic sites. This selection will also be systematic: we will enumerate every male and female in the HIV care registers and then systematically select men and women at pre-determined intervals. The selection interval (for example, every fourth woman listed) will differ by clinic depending on the total number of male and female adult registry entries. Because clinic registers are more complete for ART patients than for pre-ART patients (those not yet eligible for ART), we assume that the large majority of patients recruited from the registers (upwards of 90 %) will have qualified for ART. Therefore, we aim to recruit 75 % of our participants through the first strategy and 25 % of participants through the second strategy to ensure that non ART-qualifying participants are included.

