## Trial status

The trial began recruitment in one of two study sub-districts on 20 October 2014 and in the second sub-district on 26 January 2015. We aim to complete recruitment by 5 January 2015.

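### Under the protocol's revised eligibility estimate, the 75/25 recruitment mix is expected to yield at most 17.5–25% not-yet-eligible participants after the guideline change, below the stated 30% minimum

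*Protocol article*

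**What the plan says.** All the figures are in the Protocol article, under Participant eligibility and recruitment, except the dates.

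- **Target composition.** The sample is to have "substantial representation (minimum of 30 %) of clients who do not yet quality for ART", so that linkage and retention can be assessed both in clients who start ART and in those who do not. Total enrolment is 750.
- **Means of reaching it.** There are two recruitment routes. The first takes people at HIV testing or at collection of an initial CD4 result. The second samples the HIV care registers. The section states that "we aim to recruit 75 % of our participants through the first strategy and 25 % of participants through the second strategy" and gives as the reason that participants who do not qualify should be included.
- **Initial estimate, first route.** The investigators expected that "between 50 % and 60 % of those recruited during HIV testing would have an ART-qualifying CD4+ cell count".
- **Revised estimate, first route.** After the national threshold rose to 500, they think it more likely that 70 to 80% of "individuals newly diagnosed after January 2015 will qualify for ART".
- **Registers.** Upwards of 90% of register recruits are assumed to have qualified.
- **Dates (Trial status).** Recruitment opened in one sub-district on 20 October 2014 and "in the second sub-district on 26 January 2015".

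Neither the 30% minimum nor the 75/25 mix is revised after the new estimate is introduced. The article states no quota or cap on eligible participants.

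**The concern.** The mix is presented as the means of securing the minimum, and it appears to have been set using an estimate that the same section then replaces. Both routes select without regard to CD4 count: the first approaches everyone presenting, and the second takes men and women at fixed intervals. The mix is therefore the only stated control over the pre-ART share. If the expected qualifying proportion rises and the mix stays the same, the pre-ART share has to fall.

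What is at stake is a stated feature of the sample and the purpose attached to it. Retention, the primary outcome, has its own definition for people not yet eligible (repeat CD4 testing; Measures and Table 1). A smaller pre-ART group means less precise description of retention and linkage in that group than the 30% figure leads a reader to expect.

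**Working it through.** **Inputs** (Participant eligibility and recruitment): weights of 0.75 for the first route and 0.25 for the registers; share not yet eligible in the first route of 0.40–0.50 (initial) or 0.20–0.30 (revised); share not yet eligible in the registers of at most 0.10.

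**Formula.** Pre-ART share = 0.75 × (1 − q1) + 0.25 × (1 − q2), where q1 and q2 are the proportions qualifying for ART in the two routes.

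**Step 1: reproduce the plan's 30%.** Under the initial estimate with q2 = 0.90:
- 0.75 × 0.40 + 0.025 = 32.5%
- 0.75 × 0.50 + 0.025 = 40.0%

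With q2 = 1 the range is 30.0–37.5%. The minimum is met, and 30% is exactly the floor.

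**Step 2: the revised estimate.** With q2 = 0.90:
- 0.75 × 0.20 + 0.025 = 17.5%
- 0.75 × 0.30 + 0.025 = 25.0%

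The whole range is below 30%, by 5 to 12.5 points. Because the register figure is upwards of 90%, this is the generous case; with q2 = 1 the range is 15.0–22.5%.

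**Step 3: in participants.** The minimum is 0.30 × 750 = 225. If all 750 fell under the revised estimate (an assumption), the expected number is 0.175 × 750 = 131 to 0.25 × 750 = 188.

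**Step 4: allow for recruits before the change.** Let f be the share of first-route recruits to whom the initial estimate applies. The document does not give f. Overall share = 0.025 + 0.75 × [f × a + (1 − f) × b], where a is the initial and b the revised share not yet eligible.

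| f (assumed) | Unfavourable ends (a = 0.40, b = 0.20) | Midpoints (0.45, 0.25) | Favourable ends (0.50, 0.30) |
|---|---|---|---|
| 0 | 17.5% | 21.3% | 25.0% |
| 1/4 | 21.3% | 25.0% | 28.8% |
| 1/3 | 22.5% | 26.3% | 30.0% |
| 1/2 | 25.0% | 28.8% | 32.5% |

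To reach 30%, the first route must average (0.30 − 0.025)/0.75 = 36.7% not yet eligible, so f = (0.367 − b)/(a − b). This gives 33% at the favourable ends, 58% at the midpoints and 83% at the unfavourable ends. The first route supplies 0.75 × 750 ≈ 563 people, so 33% is about 188 of them.

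**Step 5: can the mix be adjusted?** With registers at 10%, moving 10 points of recruitment to the first route adds 0.10 × (0.20 − 0.10) = 1 point to 0.10 × (0.30 − 0.10) = 2 points. Recruiting everyone through the first route gives 20–30%, which touches the minimum only at its most favourable end.

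**The case against.** The strongest reply is that the minimum applies to the whole sample, whereas the 70–80% figure applies only to people diagnosed after January 2015. One sub-district had been recruiting since 20 October 2014, and those recruits fall under the more favourable estimate. This stands. A reader might infer that the mix cannot deliver 30% at all. The document does not support that, because step 4 shows that enough early recruitment could bring the average to 30%. The share recruited before the change cannot be worked out: enrolment by sub-district is not given, and the printed completion date (5 January 2015) precedes the second sub-district's opening.

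The boundary is also less sharp than it looks. The revised figure is tied to date of diagnosis, and people returning for an initial CD4 result may have been diagnosed earlier. Applying 20–30% to every first-route recruit after the change is a reasonable simplification, but it is an assumption. The second sub-district opened late in January 2015, so it is close to wholly under the revised estimate, but the text does not establish that it is entirely so.

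A reader might also infer that the pre-ART group becomes too small for the primary outcome, or that a confirmatory pre-ART analysis is lost. Neither follows. Sample size estimation concerns retention in the whole evaluable sample of 600. The article states no power or precision target for pre-ART participants and describes no separate confirmatory analysis in them.

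Finally, the article openly reports the guideline change and the new estimate. That makes this a missing consequential update. It does not remove the inconsistency, because the minimum and the mix remain current text beside the new figure.

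**Conclusion.** The point holds as an internal inconsistency. For people recruited under the revised estimate, the stated mix is expected to give at most 17.5–25% not yet eligible, against a stated minimum of 30%. The mix met that minimum only under the superseded estimate.

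The 17.5–25% rests on the article's own figures plus one assumption, that the revised estimate applies to all first-route recruits after the change. The count of 131–188 against 225 needs the further assumption that all 750 were recruited under it. For the sample as a whole a shortfall is likely but not proven. At the midpoints, more than half of first-route recruits (58%) would have to predate the change, while one of the two sub-districts opened only on 26 January 2015.

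The consequence is lower precision for pre-ART linkage and retention than the 30% figure implies. Nothing here shows that the primary comparison in all participants is underpowered.

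**What to change.** Reconcile the 30% minimum, the 75/25 mix and the revised estimate in Participant eligibility and recruitment:

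- Replace the 30% minimum with the expected not-yet-eligible share: 17.5–25% among those recruited after the change.
- State what proportion of first-route recruits predates the change, and give the overall expected share that follows from it by the formula in step 4. Correct the completion date in Trial status so that the recruitment period can be read.
- Add a sentence acknowledging that linkage and retention in pre-ART participants will be estimated with less precision than a 30% share would have allowed.

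Shifting recruitment from the registers to the first route can be considered, but at 1–2 points gained per 10 points moved, and 20–30% at most, it is not a dependable way to restore the minimum.

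The cost is a change of wording and a less favourable stated figure. No extra patients are needed.

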### Analysis

Our preliminary analysis will include presentation of participant demographic characteristics, service usage, acceptability of intervention approaches and self-reported sexual behavior within each of the three study arms using descriptive statistics (one-way and cross-tabular frequency tables and, for continuous variables, measures of central tendency). Measures of variability will account for repeated measures (multiple patients) and consequent correlation of variables (clustering) within each health facility. We will employ multiple imputation (MI) using chained equations to account for missing data. This procedure assumes that incomplete data arise from a missing-at-random (MAR) process, under which missingness is random conditional on observed covariables and observed outcomes rather than a missing-completely-at-random (MCAR) mechanism [43], thus making fewer assumptions about the nature of the missing data. We will conduct sensitivity analysis using weighted MI to evaluate the robustness of the MAR assumption [44].

Our primary analyses will employ an intention-to-treat (ITT) approach. We will employ logistic generalized estimating equations (GEE) to compare patient retention between intervention arms. We will also evaluate secondary outcomes (linkage, adherence and prevention behaviors) using an ITT analysis, as described above. We will employ GEE rather than mixed effects models as this approach allows us to estimate the effect of the intervention at the level of the population, rather than at the level of the individual. As our interventions will be implemented at the level of the health system, it is important to estimate the effect of the intervention at the level it is implemented [45]. Further, previous research has suggested that adjustment for confounding can improve the efficiency of estimates in the context of randomized trials [46]. We will thus conduct sensitivity analyses employing causal inference methods to account for any imbalance in distribution of site- and individual-level co-variables across study clinics. We will employ targeted maximum likelihood estimation [47], which allows estimation of both site- and individual-level co-variables, to minimize bias and improve efficiency of estimates of effect in the context of small sample sizes [48].

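### Participants enter from two recruitment streams after clinics are randomised, but the article places adjustment for individual-level imbalance only in a sensitivity analysis; it belongs in the primary model

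*Protocol article*

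**What the plan says.** Under Study design, allocation is complete while enrolment is still to come: "Clinics have been randomized to one of three conditions". Participant eligibility and recruitment then describes two streams.

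- **Testing stream.** "all of those presenting for an HIV test or for an initial CD4+ test result will be approached by clinic staff". After the change in guidelines, 70 to 80% of the newly diagnosed are expected to qualify for ART (50 to 60% before it).
- **Register stream.** Study staff enumerate the care registers and "systematically select men and women at pre-determined intervals", with an interval that varies by clinic. Upwards of 90% of these recruits are expected to have qualified for ART.

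The mix is given once: "we aim to recruit 75 % of our participants through the first strategy and 25 % of participants through the second strategy". The sex aim is "We aim to recruit an equivalent number of men and women". The only target stated explicitly per clinic is a head count, "with a target of 42 (range = 30-55) participants at each facility".

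The notes to Fig. 1 report that one clinic assigned to SMS had not opened on schedule; "as such, recruitment targets have been adjusted at the remaining SMS clinics". Under Measures, retention means staying on treatment for patients on ART and having repeat CD4 tests for those not yet eligible.

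Under Analysis, the primary comparison is a logistic GEE by arm with no covariates named. Adjustment of the intention-to-treat comparison follows as: "We will thus conduct sensitivity analyses employing causal inference methods to account for any imbalance in distribution of site- and individual-level co-variables", by targeted maximum likelihood estimation.

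**The concern.** In a cluster trial, randomisation balances clinics. It does not by itself balance a participant mix that forms after allocation. Here the mix plausibly predicts the primary outcome. A register recruit has already reached care, whereas a first-time tester may still drop out before linkage. The two streams also differ in how many are judged by the treatment definition of retention rather than the CD4 definition.

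If one arm takes a larger share from registers, the unadjusted comparison attributes part of that difference to the intervention. With four control clinics, a single clinic counts heavily: a 40-point shift in one clinic's register share moves the arm by 10 points. The article foresees individual-level imbalance and names a method for it, but leaves the headline estimate outside that protection.

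**Working it through.** **1. The plan's own figure.** Inputs from Sample size estimation: 750 enrolled, 20% attrition, 18 clinics, 50% retention under standard of care, two-sided alpha 0.05, 80% power, intra-cluster correlation (ICC) 0.0225 to 0.04.

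- Evaluable: 750 × 0.80 = 600, or 600/18 = 33.3 per clinic.
- Design effect = 1 + (m − 1) × ICC. A two-proportion calculation then gives detectable differences, intervention (7 clinics) against control (4), of 19.4 to 22.1 points at m = 33.3 and 20.0 to 22.6 at m = 30. For 7 against 7 clinics at m = 30 it gives 17.2 to 19.6.
- The stated 20 to 23 and 17 to 20 points are therefore reproduced. The first pair is the yardstick for SMS against control.

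**2. Places to be replaced in the SMS arm.** The article does not state the adjusted targets. Assuming that the arm total is kept:

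- SMS arm: 750 × 7/18 = 291.7. Per clinic: 291.7/7 = 41.7.
- With six clinics: 291.7/6 = 48.6 each, within the planned range of 30 to 55.

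**3. Register share if those places come from registers alone** (an extreme case):

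- Six clinics at the planned mix: 250 × 0.25 = 62.5 register recruits.
- Missing clinic's places: 41.7 register recruits.
- SMS register share: (62.5 + 41.7)/291.7 = 35.7%, against 25% in control. The difference is 10.7 points.
- If both other arms stay at 25%, the trial-wide share becomes (104.2 + 41.7 + 72.9)/750 = 29.2%, so the overall aim is overshot.

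**4. Spurious difference** = difference in register share × difference in retention between streams. The documents give no retention by stream, so 10 to 30 points is assumed:

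- 0.107 × 0.10 = 1.1 points
- 0.107 × 0.20 = 2.1 points
- 0.107 × 0.30 = 3.2 points

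**5. Against the precision of the trial.** Standard error for 7 against 4 clinics = √[0.25 × design effect × (1/133.3 + 1/233.3)].

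- ICC 0.0225: design effect 1.73, standard error 7.1 points.
- ICC 0.04: design effect 2.29, standard error 8.2 points.

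A bias of 1 to 3 points moves the nominal 5% error to about 5 to 7%.

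**6. How much runs through ART status.** With 90% qualified from registers and 70 to 80% among testers, a 10.7-point shift in source changes the ART-qualified share by 0.107 × 0.10 = 1.1 to 0.107 × 0.20 = 2.1 points. Adjusting for ART status alone would therefore not capture the whole difference between streams, which is why source is also needed.

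**7. Can the mix be relied on to stay at 75/25?** With those percentages it yields 0.75 × 0.20 + 0.25 × 0.10 = 17.5% to 0.75 × 0.30 + 0.25 × 0.10 = 25% not yet qualifying, below the stated minimum of 30%. The two aims conflict, so some drift in the mix is to be expected. This pressure works towards fewer register recruits.

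**The case against.** The strongest reply is that this is a condensed article. Clinic quotas for source and sex, and a covariate list, are details that a fuller protocol or analysis plan would hold. Selection within each stream is systematic: everyone in the testing stream is to be approached, and registers are sampled at fixed intervals by sex. Clinics were screened for patient load, and randomisation was restricted on HIV tests and ART numbers, which relate to the size of both streams. The streams also overlap: register recruits are recent entries, everyone is within a year of diagnosis, and the testing stream includes people returning for a CD4 result.

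Most of this stands, and it rules out several stronger readings.

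- **That the source mix and sex balance are whole-trial quotas.** The article gives no level of application. The sex part is weaker still, since register selection is already by sex.
- **That SMS clinics top up from registers, or that recruiters steer by allocation.** Neither is stated. Register selection is done by the study team.
- **That the SMS clinic never opened.** The note says only that it had not opened when scheduled.
- **That the bias reaches 3 to 6 points.** This needs register shares such as 25% in control against 40% in SMS, or 20% against 40%. To keep 25% overall (187.5 of 750), peer navigation would have to sit at (187.5 − 41.7 − 116.7)/291.7 = 10%, or (187.5 − 33.3 − 116.7)/291.7 = 13%. Nothing in the article points to that.

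What the reply does not answer is the placement of the adjustment. The safeguards govern selection within a stream, not the ratio between streams. The article does not merely omit a covariate list: it assigns correction of imbalance in the intention-to-treat comparison to a sensitivity analysis, while noting itself that adjustment can improve efficiency.

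**Conclusion.** The point holds as a modest, specific improvement to the primary analysis. Enrolment follows allocation, the mix of two unlike streams is not shown to be fixed by clinic or arm, one arm's targets changed after allocation, and the outcome definition depends on ART status. The primary model as described has no stated protection against the resulting imbalance.

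On the one pressure that the article documents, the spurious SMS-versus-control difference is about 1 to 3 points. That is at most about 15% of the detectable difference (3.2/20 = 16%; 3.2/23 = 14%) and less than half a standard error. This rests on three assumptions: the SMS arm keeps its total, all replacement places come from registers, and retention differs by 10 to 30 points between streams. The first two are not stated and the third has no source in the article. The trial's conclusions are not shown to be at risk; the case for change is that the remedy costs almost nothing.

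**What to change.** In Analysis:

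- Make the primary logistic GEE adjust for ART status at enrolment and sex, both captured at enrolment according to the Intervention section, and for recruitment source (testing or register).
- No passage says that source is recorded. Confirm that it is, or derive it from time since diagnosis and date of register entry.
- Keep the unadjusted GEE as a sensitivity analysis alongside targeted maximum likelihood.
- Report the source mix, with sex and ART status, by arm.

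In Participant eligibility and recruitment, for the enrolment that remains, aim for the 75/25 mix within each clinic where feasible: about 32 and 10 of 42, or 37 and 12 of 49. This is the weaker part of the remedy. Recruitment had already begun, so it should be an aim rather than a hard cap, and a clinic with few new diagnoses may fill more slowly.

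Costs: a few extra parameters with 17 or 18 clusters. The adjusted odds ratio is also conditional on the covariates, whereas the article chose GEE for a population-level effect. Standardising the adjusted estimate over the covariates restores the marginal effect. Adjustment handles only measured differences between recruits. The sample-size inputs are unchanged.
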